### Data Analysis

Abnormal test results will be determined using the criteria adapted from Leat et al (Table 2) [17].

To establish the prevalence of BV disorders, the proportion of abnormal test results will be reported and compared by age group, dementia severity, and dementia type as well as against the data in Leat et al [17]. Pupillometry measures (maximum dilation velocity, average dilation, and minimum/maximum size) for high and low cognitive loads will be similarly compared with age-related norms collected in a separate study of adults aged 50 years with a normal standardized MMSE score (>26 out of 30) using the same paradigm.

MRI data will be visually inspected for quality, and participants with excessive head motion (>3 mm in any axis or >3) will be excluded. Functional MRI data will be preprocessed and analyzed in SPM8 (Wellcome Department of Imaging Neuroscience) using the standard generalized linear model approach. Preprocessing will correct for slice timing and head motion. Smoothing will not be performed to preserve spatial resolution and, because of the within-subject design, spatial normalization will not be required. In each participant’s design matrix, the timing of the stimulus blocks will be entered as regressors of interest and convolved with the canonical hemodynamic response model; head motion parameters will be included as covariates of no interest. To analyze the multifocal retinotopic mapping results, the procedure outlined by Henriksson et al [53] will be followed: coregistration between anatomical and functional data will be performed in SPM before transfer to Freesurfer using each participant’s T1-weighted structural scans and the preprocessed functional MRI data. Eccentricity and polar angle retinotopic maps will be visualized using Freesurfer and used to denote regions of interest (ROIs) for primary visual areas V1, V2, V3, V4, and V3A. For stereoscopic image viewing, within-subject change between the first and final visits in the regional BOLD signal will be calculated for occipital and parietal lobe ROIs. Structural analyses will be conducted using Freesurfer; changes in cortical thickness in the occipital and parietal lobe ROIs and changes in the medial temporal lobe volumes will be calculated at the within-subject level.

## Results

### Current Status

This research was funded in February 2018 and received approval from the NHS Research Ethics Committee in September 2018. The data collection period was from October 1, 2018, to November 30, 2019. A total of 24 participants were recruited for the study. Data analysis is complete, and the results are expected to be published before the end of 2020.

### Anticipated Impact

Binocular, visual, and pupil function tests are routine, low-risk, quick, and noninvasive; if found to be interlinked markers of cognitive decline, monitoring their change over time could be an important aspect of future dementia care. Orthoptists, as allied health professionals, are well-placed to take on this role because of their ability to conduct objective assessments of visual function in people with cognitive difficulties, thereby obtaining robust clinical data.

If BV disorders are found to be more prevalent in this group than in older people, further research could explore the impact of treating BV disorders on quality of life for PWD and their caregivers, potentially evidencing to commissioners the need for dedicated orthoptic services for PWD. This would also provide evidence for the inclusion of assessment and treatment of BV disorders within the College of Optometrists [56] and Royal College of Ophthalmologists [57] dementia guidelines and the proposed Dementia Eye Care Pathway [58], where it does not currently feature.

## Discussion

### Ethical Considerations

#### Risks of Participation

All participants have a confirmed diagnosis of dementia as part of the inclusion criteria; thus, disclosure of diagnosis through study information materials has very low impact risk. All clinical tests used are noninvasive, quick, and low-risk, and, except for the ASTEROID stereotest and pupillometry, are routinely conducted in orthoptic practice with minimal distress to patients. The ASTEROID stereotest requires the participant to simply look at some dots on a computer screen and has been successfully performed with older people who have cognitive impairment in another study, with no distress (Table 1). Similarly, pupillometry measurement is simple and has been used extensively in people who have dementia or cognitive impairment in the past [30,59,60].

Medical imaging is a routine and well-accepted aspect of clinical care for people with dementia attending the participating NHS Trust’s community mental health clinics. Therefore, the inclusion of MRI scans for a subgroup of participants (n=30) is not anticipated to cause a significant burden. A panic button will be provided for the participant to use and their caregiver will be able to communicate with them via intercom during the scan, to provide reassurance.

If a symptomatic BV problem is diagnosed at the baseline visit, or VA deteriorates by a clinically significant amount during the study period (ie, reduction >0.200 logMAR), a report letter will be generated and sent to their general practitioner (GP) or optometrist. This allows participants, if they wish, to initiate further investigation or seek onward referral to the hospital eye service to explore treatment options. Similarly, if a gross abnormality is identified on MRI scanning, a letter will be sent to the GP, copied to their memory clinic consultant if appropriate, to prompt further investigations. This is per the standard operating procedures for the MRI facility.

Symptomatic BV disorders are associated with an increased risk of falls [14]; therefore, providing the option to seek further treatment is an important ethical consideration to mitigate this risk. As the study is exploratory and examining the relation between changes in the parameters of interest over time, rather than the etiology underlying such changes (eg, initiation of orthoptic treatment), it is still possible to include data from participants who have sought onward referral or received orthoptic treatment within analyses.

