### Procedures

Informed consent will be sought from participants or a consultee process will be employed where appropriate, with the capacity to consent determined by a validated brief questionnaire [50] where indicated. Ongoing consent [51,52] will be determined on a per-visit basis. The consent form also includes provisions for the participant to express their wishes concerning participation in the study, should they experience a loss of mental capacity before the study is completed, as an adjunct to these considerations.

A case history (caregiver supported if required), including dementia type and diagnosis date, ensures eligibility criteria are met. Dementia type and diagnosis date, previous ocular history, and previous imaging findings will be corroborated using the patient’s medical records after consent is obtained.

Eligibility screening is supported by optometric information (VA, current prescription, and fundus/media check findings), obtained from the patient's optometrist, or a monocular distance VA test if the last NHS sight test was >1 year ago. If the latter satisfies the eligibility criteria, an updated sight test can be arranged by the researcher (by written agreement) or the participant or their caregiver with a provider of their choice. If eligible to participate, the researcher will contact the participant to organize the initial study visit as well as an MRI scan if eligible.

All participants will be invited to complete the Pittsburgh Sleep Quality Index at each study visit—or this can be proxy-completed by a caregiver with knowledge of the participant’s sleep patterns.

The following clinical tests will be performed at a community clinic or in the participant’s home by the researcher (registered orthoptist) at all study visits:

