The testing time is approximately 60 min in total (including computer setup), with breaks offered if required. All tests are low-risk, quick, noninvasive, and (except for pupillometry) routinely performed in orthoptic practice.

All participants will return for 2 follow-up assessments, 4 months apart (plus or minus 2 weeks), repeating the above tests. Adaptations required to enable performance of a test will be documented, for example, change in test target, use of matching card, demonstration of testing procedure, and instances where performing tests was not possible.

The MRI subgroup (n=30; diagnosis of Alzheimer disease) will also receive an MRI scan (within 2 weeks of the first and final study visits) using a 3T TIM Trio MR scanner (Siemens) with a 32-channel array head coil.

Whole-brain scans performed included the following:

Structural MRI (11 min in total): T1-MPRAGE, FOV 192 mm, matrix 256 × 256, 1 mm isotropic spatial resolution, TR=2250 ms, TE=2.98 ms, flip angle 9°, GRAPPA factor 2, and acquisition time 4 min 32 seconds.
T2-TSE, 29 × 4 mm slices, slice gap 1.2 mm, FOV 220 mm, matrix 320 × 320, 0.7 mm isotropic spatial resolution, TR=5060 ms, TE=102 ms, flip angle 140°, GRAPPA factor 2, acquisition time 1 min 38 seconds
FLAIR-TSE, 25 × 4 mm slices, slice gap 1.2 mm, FOV 220 mm, matrix 256 × 256, 0.9 mm isotropic spatial resolution, TR=9000 ms, TE=100 ms, flip angle 150°, acquisition time 4 min 32 seconds.Functional MRI (25 min in total): BOLD T2–EPI, 32 × 3 mm descending slices, slice gap 0.75 mm, FOV 192 mm, matrix 64 × 64, voxel size 3 × 3 × 3 mm, spatial resolution 3 mm × 3 mm, TR=2000 ms, TE=30 ms, flip angle 78°, bandwidth 2112 Hz per pixel, echo spacing 0.54 ms.

Viewing comprised the following:

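### The report letter for a symptomatic binocular vision problem is tied to the baseline visit, although binocular vision is tested at all three visits and the fall-risk reason applies at each

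*Protocol article*

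**What the plan says.** The Protocol article deals with clinical findings under Discussion, Ethical Considerations, Risks of Participation. A letter goes to the GP or optometrist on either of two conditions: "If a symptomatic BV problem is diagnosed at the baseline visit, or VA deteriorates by a clinically significant amount during the study period". The VA condition is defined as a reduction of more than 0.200 logMAR. A separate letter to the GP follows a gross abnormality on MRI, with no visit named.

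The same section then gives the reason. Symptomatic BV disorders carry a raised risk of falls, so "providing the option to seek further treatment is an important ethical consideration to mitigate this risk". It adds that, because the study is exploratory, "it is still possible to include data from participants who have sought onward referral or received orthoptic treatment within analyses".

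Methods, Procedures, has the clinical tests performed "by the researcher (registered orthoptist) at all study visits". The list includes the cover test, suppression, ocular motility, prism fusion range, stereotests, near point of convergence and prism cover test. The schedule then states: "All participants will return for 2 follow-up assessments, 4 months apart (plus or minus 2 weeks), repeating the above tests".

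**The concern.** The two triggers sit in one sentence but have different time scopes, and the BV scope is narrower than the reason given for it. The study looks for BV problems three times, yet its written duty to report a symptomatic one attaches only to the first.

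At stake is the protection of a participant whose problem appears during follow-up, for example a new heterotropia with double vision at month 4. That person has the fall risk the protocol wants to mitigate but is not assured the letter that opens the way to treatment. New problems are plausible: the first aim is to track change in binocular function, and the Introduction says that oculomotor control is disrupted in some dementias and that BV problems of this origin are often remediable with simple treatments. The protocol also foresees loss of capacity during the study, so relying on participants to seek help themselves is a weak substitute for a letter.

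**Working it through.** No power, sample size or error-rate figure is involved. The check is a count of visits and a comparison of the rule with its reason.

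**Inputs**

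- BV test visits: baseline plus 2 follow-ups 4 months apart (Procedures).
- BV trigger: "If a symptomatic BV problem is diagnosed at the baseline visit" (Risks of Participation).
- VA trigger: "VA deteriorates by a clinically significant amount during the study period" (same sentence).
- Participants: "A total of 24 participants were recruited for the study" (Results, Current Status); maximum target 210 (Study Design and Recruitment).

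**Count**

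- BV test visits per participant: 1 + 2 = 3, at about months 0, 4 and 8.
- Named by the BV trigger: 1. Not named: 3 − 1 = 2.
- With 24 participants: 24 × 3 = 72 planned occasions, of which 24 × 2 = 48 lie outside the trigger.
- At the maximum of 210: 210 × 3 = 630 planned, 210 × 2 = 420 outside.

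These counts assume full attendance, so they are upper bounds. They count visits, not cases.

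**Rule against reason**

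| Element | Time scope in the text |
|---|---|
| BV testing | All 3 visits |
| Fall-risk reason for offering treatment | No visit named |
| VA letter | Whole study period |
| MRI letter | No visit named |
| BV letter | Baseline visit |

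Only the last row is restricted.

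**Could protecting the analysis explain the limit?** No. The section says that referred or treated participants can stay in the analyses. Moreover, no further clinical assessment follows the third visit, yet that visit is also outside the trigger.

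**Do other routes close the gap?** Only in part. A participant who also loses more than 0.200 logMAR of VA, or whose scan shows a gross abnormality, gets a letter. A symptomatic BV problem with neither does not, as the text stands. MRI is in any case confined to the subgroup (planned n = 30).

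**The case against.** The strongest reply is that this is loose drafting and not a decision to leave out later cases. The sentence does not say that baseline is the sole occasion. VA deterioration needs an earlier value and so can arise only during follow-up, whereas a BV problem can be found at the first full assessment; the two time phrases may simply mark when each is first expected. The text sits in the Discussion of a condensed article, and the full protocol may provide for later visits. A registered orthoptist might well write a letter whatever the article says.

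Part of this stands. Later letters are not forbidden, and nothing in the article shows that any was withheld. The visit counts say nothing about the number of people harmed. The 420 of 630 figure concerns a sample that was not reached, and even 48 may be too high. Data collection ended on November 30, 2019. Two intervals of 4 months, each shortened by the permitted 2 weeks, come to 8 months less 4 weeks, so anyone enrolled after about late April 2019 could not have had a third visit on schedule.

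The reply does not remove the mismatch. The article is not silent about timing: it states a visit, and states a different scope for VA in the same sentence. Staff who follow the text have no instruction to send a letter for a BV problem first found later. Loose drafting, if that is what it is, calls for the same correction.

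**Conclusion.** The concern holds as a minor inconsistency in participant safety. The BV letter is required on the findings of 1 of the 3 visits at which BV is tested, while the reason behind it applies at all 3.

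For the 24 recruited participants, at most 48 of 72 planned test occasions are uncovered, assuming full attendance. The article gives neither the incidence of new symptomatic BV problems nor follow-up attendance, so the number of participants affected cannot be computed and may be zero. The conclusion rests on the text as written and on the article containing no other provision for such a letter; the full protocol was not available. Sample size and statistical analysis are unaffected.

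**What to change.** 1. Under Risks of Participation, make the BV trigger apply to a symptomatic problem diagnosed *at any study visit*. Coverage then goes from 1 of 3 to 3 of 3 BV test visits and matches the fall-risk reason.
2. Because data collection has ended, the wording alone helps no one already enrolled. Check the visit 2 and visit 3 records of the 24 participants for symptomatic BV problems first found then, confirm that a letter was sent, and send one where it was not.

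The cost is one phrase, a review of at most 48 visit records, and at most one letter per participant for a first-found problem. No new test or staff is needed, and by the protocol's own account referral or treatment does not bar a participant's data from the analyses.

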#### Financial Incentives

A nominal honorarium shows recognition and appreciation of the time and effort made by participants to attend study visits and undergo testing. As study participation involves 3 study visits and, for some participants, 2 additional visits for MRI scans, it was felt that including this honorarium was appropriate to acknowledge this burden of participation. Travel expenses are also reimbursed to ensure participants are not left out of pocket by participating in the research.

It is recognized that as part of the Health Research Authority (HRA) guidance on payments for research [61], incentives or financial inducements should not be offered where adults cannot consent. Although the research is limited to individuals with a diagnosis of dementia made in the last 24 months, there may be instances where ongoing consent changes or diagnosis is made after dementia has substantially progressed. The University of Surrey’s Research Integrity and Governance Office will also provide input and advice in these instances. Procedures regarding honorariums are explained within the study information materials.

#### Data Protection and Confidentiality

All participants will be assigned a number upon entry to the study. All paper and digital study records will use this number instead of the participant’s name to preserve anonymity. Paper project data (related to the administration of the project, for example, consent forms and record sheets) will be kept in a locked filing cabinet in a lockable room in the R&D office at the participating NHS Trust. Electronic data (primarily data sets) will be stored and pseudonymized by participant number on the university’s secure research storage server for a minimum of 10 years. Data will be disposed of securely via confidential shredding or electronic formatting after these times.

Participants will not be personally identifiable in any publication material. Participants can give permission on the consent form for their anonymous data to be deposited in a repository. Participants will be able to withdraw their data, without giving a reason, until the point at which their data is published in an anonymized form.

Anonymous data may be published with consent in data repositories (eg, Dementias Platform UK or the UK Data Archive) or as required by scientific journals to accompany article publication. These data may contain raw data or summary data (eg, means and SDs) from any measures collected. No identifiable information (eg, names, date of birth, etc) will be published. Anonymous data may be used for future research purposes by the research team or other researchers, provided the research has ethical approval.

### Patient/Public Involvement

Study information materials have been developed with 3 patient involvement representatives who have dementia or care for someone with dementia. Designing study materials with this patient group ensures that they are suitable for use in the informed consent process. This involvement work supported timely ethics review and has also assisted in developing the best method of approaching people with dementia to participate in the study.

We consulted with our involvement representatives about several issues pertaining to the study, such as the best approach toward eligibility screening and redistribution of funds allocated for honorariums where a participant does not have the capacity and is unable to receive it. We also sought advice from the patient involvement staff at the Alzheimer’s Society to ensure that our approach reflected best practices.

For honorariums, it was recommended that a discussion take place at the point of entry to the study, in instances where the participant has capacity to consent, to establish their preferences for distribution of the honorarium in the event that their capacity deteriorates. Another alternative suggested where capacity was not present at the point of enrolment in the study was reallocating the honorarium amount toward reimbursement of other costs associated with study participation as appropriate, for example, meal vouchers and increased travel budget.

For eligibility screening, our representatives shared their experiences of having their eyes tested and felt that offering to organize the test would be acceptable to avoid inducing the burden of participation, provided potential participants and their caregivers are also given the option to organize their own test if they wish and they have given consent for contact details or test results to be exchanged for this purpose.

Our patient involvement volunteers remain involved throughout the study, with additional patient involvement meetings scheduled for after data collection, to discuss any issues with the recruitment approach or study methods that may require an amendment, and at the end of the study to present the findings, establish the key take-home messages relevant to people with dementia and their caregivers, and to develop a lay summary of the findings. The Health Research Authority and INVOLVE patient involvement standards [62] were used to develop the initial recruitment materials and information pack for being involved in the study and are being used for communications with our involvement representatives throughout the study. HRA guidance on discussing public involvement embedded within the Integrated Research Application System application form was also followed.

## Abbreviations

BOLD: blood oxygenation level dependent
BV: binocular vision
GP: general practitioner
HRA: Health Research Authority
MMSE: Mini Mental State Examination
MRI: magnetic resonance imaging
NHS: National Health Service
NPC: convergence near point
PFR: prism fusion range
PSR: Preschool Randot
PWD: people living with dementia
R&D: research & development
ROIs: regions of interest
VA: visual acuity
